### Study design

The study is organized as a mixed-methods study [41] with different methodological components (sections A-D). The leader of the study is the Institute for Social Medicine and Epidemiology of the University of Lübeck. The recruitment takes place in five different rehabilitation clinics in Germany (AMEOS Reha Klinikum Ratzeburg, Klinik Graal-Müritz, Strandklinik Ostseebad Boltenhagen, Asklepios Klinik Am Kurpark Bad Schwartau, Sonneneck Nordsee-Fachklinik Wyk auf Föhr). The designated aftercare agents of each clinic are responsible for the screening of eligible patients within the first days of their rehabilitation. If applicable, the agents address the patients personally and give them the information sheets and the declaration of consent.

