### A: quantitative measures

To examine the long-term effects of oncological rehabilitation with ReNaApp, the study is structured as a monocentric, quasi-randomized longitudinal study with three measurement points: at the beginning (t_0_) and end of rehabilitation (t_1_) and 12 months after rehabilitation (t_2_). All patients will complete a written questionnaire using standardized, validated instruments.

Following a sequential design, all rehabilitants who arrive in the rehab clinics belong to the control group (standard therapy and standard aftercare) until the desired number of cases is reached. After the recruitment of the control group, the rehab teams of all clinics are instructed in the handling of ReNaApp and the aftercare philosophy. The implementation of the aftercare intervention is accompanied by a fundamental change in the procedures and therapy regimens in clinics; therefore, recruitment of the control and intervention groups at the same time will not be possible. The later rehabilitants who fulfil the eligible criteria will be allocated to the intervention group. Based on preliminary interviews in rehab clinics, we assume that most of the rehabilitants own a smartphone and know how to use a mobile application.

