### Case number calculation/sample size

According to the time and primary outcomes, we expect that both groups (control and intervention groups) will similarly improve until the end of rehab. In the following period, the effects in the CG will approach the starting level before rehab, while the positive changes in the IG will stabilize and even increase slightly. We assume that the intervention group will return to work with higher likelihood and earlier than the CG.

Regarding the needed sample size, the primary outcome *restriction in participation* (IMET [42]) will be involved. For this purpose, we have results from our own studies about the influence of “Neues Credo”. To determine the effect of data on the Quality Community for Medical Rehabilitation (QGmR, indication oncology) [52], the controlled trial of “Neues Credo” [14] and the feasibility study of “Neues Credo” [15] were taken into account.

The QGmR data from oncological patients who followed a standard rehab and standard aftercare did not show an effect (ES = 0.05) on participation after a four-month follow-up. The IG participation in the controlled trial of “Neues Credo” showed an effect intensity of ES = 0.42 in a 12-month follow-up, and the control group showed an effect intensity of ES = 0.06. Psychosomatic rehabilitants reached an effect intensity of ES = 0.53 for participation after a four-month follow-up in the feasibility study of “Neues Credo”.

Calculating the sample size, we assume clinically relevant and positive effects (pre-catamnesis-ES = 0.40) in *social and work-related participation* (IMET [42]) in the IG after a 12-month follow-up. Compared to the intervention group, the control group does not show any effects to the point of catamnesis. The other two primary outcomes are expected to show comparable effect intensity [79–81]. To demonstrate differences between the IG and CG after a 12-month follow-up, we require a magnitude of ES = 0.40 by double-sided testing with α = 1.6% (Bonferroni correction for three primary outcomes) with a power of 80%. That is why the intervention and control groups need a net sample size of *n* = 235 for each. We expect a dropout rate of 30% from patients with oncological rehab (according to experiences in QGmR oncology). To analyse each group of n = 235 patients, we must initially recruit 336 participants for the study; i.e., every rehab clinic has to recruit 112 participants (56 participants in each group).

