With propensity score matching (PSM), it is possible that not all participants will have a match despite the use of a caliper. The equalization of these matching failures justifies a 10% higher sample size; thus, 740 patients must be recruited (*n* = 370 for IG and CG). Taking into account that 30% of those asked will refuse to participate in the study, 528 patients of each group must be addressed to participate in the study. In summary, each clinic will address *n* = 176 patients, 88 patients in each group. Because the study does not examine differences between the clinics, the rehabilitants of each clinic will be considered as one group at the end of recruitment.

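### Pooling the five clinics because clinic differences are not a research question leaves clinic as an uncontrolled potential confounder in a sequential, non-randomised comparison

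*Protocol article*

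**What the plan says.** All references are to the protocol article.

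- **Sites.** Study design: "The recruitment takes place in five different rehabilitation clinics in Germany". Section A (quantitative measures) nevertheless says that "the study is structured as a monocentric, quasi-randomized longitudinal study with three measurement points".
- **Allocation.** Section A: all arriving patients "belong to the control group (standard therapy and standard aftercare) until the desired number of cases is reached", and the intervention group follows. It adds that "recruitment of the control and intervention groups at the same time will not be possible". No stopping rule by clinic is given.
- **Clinic in the analysis.** Case number calculation/sample size: "Because the study does not examine differences between the clinics, the rehabilitants of each clinic will be considered as one group".
- **Quotas.** The same section says that "every rehab clinic has to recruit 112 participants (56 participants in each group" and, after allowing for refusal, that "each clinic will address *n* = 176 patients, 88 patients in each group".
- **Models.** Statistical methods names repeated-measures analysis of variance, contingency tables and discrete-time survival models, without a clinic term.
- **Adjustment.** Limitations foresees covariates or propensity score matching if the groups differ. The examples are participant and disease characteristics; clinic is not among them.
- **Data.** Patient documentation describes an ID made of a group digit and a running number. It mentions no clinic code.

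**The concern.** Whether clinic is a research question and whether clinic can distort the group comparison are separate matters; the pooling sentence answers only the first. Clinics may differ in case mix, therapy and region. Arm and recruitment phase coincide here, and nothing is randomised. If one clinic supplies a larger share of the intervention phase than of the control phase, its characteristics load onto the treatment contrast.

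Every clinic is planned to contribute to both phases, so comparison within clinic is available and would remove this component at little cost. A plan that sets clinic aside gives that up. At stake are some bias in the estimated effect and a type I error above the planned 1.6%.

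**Working it through.** **1. The quotas.** The sample-size chain after 235 reproduces: 235/0.70 = 335.7, so 336 per group; 336 × 1.10 = 369.6, so 370; 370/0.70 = 528.6, given as 528. (The 235 does not follow from its own inputs: effect size 0.40, two-sided 1.6% and 80% power give 133 per group. That is a separate matter; 235 is taken as stated here.)

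The quotas per clinic and group do not fit five clinics:

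- 5 × 56 = 280, not 336 (6 × 56 = 336)
- 5 × 88 = 440, not 528 (6 × 88 = 528)

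Equal fifths would be 336/5 = 67.2, 370/5 = 74 and 528/5 = 105.6. To reach the totals, some clinics must exceed their quota, and the text does not say which or in which phase.

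**2. Which outcomes are exposed.** Table 1 has IMET and disease-specific quality of life at both t0 and t2. In a group × time contrast, stable differences in clinic level cancel and only differences in change between clinics remain. Return to work is asked only at t2, so nothing cancels.

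**3. Size, under assumptions.** The article gives no intraclass correlation (ICC) and no achieved clinic mix, so both are assumed. Let d_k be the share of clinic k in the intervention group minus its share in the control group. In outcome SD units:

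- SD of bias = √ICC × √Σd_k²; 95% range = ±1.96 × SD of bias
- SE = √(2(1 − ICC)/235), which is 0.0918 at ICC 0.01 and 0.0899 at ICC 0.05
- type I error = 2Φ(−2.409 × SE/√(SE² + SD of bias²)), where 2.409 is the two-sided 1.6% critical value

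| Clinic shares, control vs intervention (%) | √Σd² | 95% range of bias, ICC 0.01 to 0.05 | Type I error |
|---|---|---|---|
| Equal in both | 0 | 0 | 1.6% |
| Mild: 20 each vs 25/22.5/20/17.5/15 | 0.079 | ±0.015 to ±0.035 | 1.6 to 1.8% |
| One clinic absent: 20 each vs 25/25/25/25/0 | 0.224 | ±0.04 to ±0.10 | 1.9 to 3.5% |
| Reversed: 30/25/20/15/10 vs 10/15/20/25/30 | 0.316 | ±0.06 to ±0.14 | 2.3 to 5.8% |

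Example, reversed mix at ICC 0.05: √0.05 × 0.316 = 0.0707; 1.96 × 0.0707 = 0.139; √(0.0899² + 0.0707²) = 0.1144; 2Φ(−2.409 × 0.0899/0.1144) = 5.8%.

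For IMET and quality of life, the ICC must be read as that of the change score. For return to work the SD scale is only illustrative.

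**4. Cost of adjusting.** Five clinics need four indicators, out of about 2 × 235 = 470 participants.

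**The case against.** The strongest reply is that the article plans a balance: equal numbers per clinic and group. If the quotas were met and the balance lasted to the analysis, the clinic-mix bias would be zero. Dropout alone would also struggle to undo it. Starting from 20% each with 70% retention, the mild shift already needs retention between 70 × 15/20 = 52.5% and 70 × 25/20 = 87.5% across clinics in one phase, with equal retention in the other. This stands as an argument that the harm may be small. It does not rescue the pooling sentence, because the quotas do not add up for five clinics and because refusal and matching failures can also vary by clinic and phase.

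Second, the pooling sentence sits in the sample-size section and may only mean that no clinic-specific results are planned; the adjustment list in Limitations is open, so clinic could still be added. That is possible. But the list concerns participants and disease and applies only if differences arise, and the one sentence about clinic points the other way.

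Four stronger readings are tempting and not supported:

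- **A bias of 11 to 20% of the effect size.** A share shift of 0.15 to 0.20 with a clinic difference of 0.3 to 0.4 SD gives 0.15 × 0.3 = 0.045 and 0.20 × 0.4 = 0.08 SD, with rejection rates of 2.9% and 6.2%. The arithmetic is right, but the shift is severe. For one clinic to fall from 20% to 5% through dropout, its retention would have to be about 15% while the others keep 70%.
- **A standard error that is too small.** With a similar mix in both arms, leaving out a clinic main effect makes the test conservative. At ICC 0.05 and equal shares, the pooled residual variance is 0.95 + 0.05 × (1 − 5 × 0.2²) = 0.99 against 0.95, and 2Φ(−2.409 × √(0.99/0.95)) = 1.4%. By the same token, the error rates under the working are slightly high.
- **Matching across clinics is planned.** The article does not say so; it only does not exclude it.
- **The word monocentric shows an analysis error.** It is a labelling contradiction and no more.

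**Conclusion.** The point holds as a weakness in a stated choice that should be corrected. The article commits to treating the clinics as one group for a reason that does not address confounding, names no clinic term in its models, and limits its conditional adjustment examples to participant and disease characteristics. The planned quotas are a real but incomplete safeguard.

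The size is unknown from the document. A mild shift in mix does almost no harm; an extreme one could more than triple the type I error. These figures rest on an assumed ICC of 0.01 to 0.05, assumed clinic mixes and 235 analysed per group. A reader should not infer that the trial's result will be materially biased: that depends on the clinic counts achieved in each phase, and the article does not give them. Return to work deserves the most attention.

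**What to change.** - Replace the pooling sentence with a statement that clinic enters every primary outcome model as a fixed factor (four indicators) and enters the propensity score.
- Leave exact matching within clinic optional. With 370 × 0.7/5 ≈ 52 completers per group and clinic, requiring it could push matching failures above the 10% allowance.
- Report the number recruited and the number analysed by clinic and phase. Adjustment can only help where a clinic has patients in both phases.
- Reconcile the quotas per clinic with the totals of 336, 370 and 528.
- Confirm that a clinic code reaches the analysis file, since the described ID contains none.
- Change monocentric in section A to multicentre (five clinics).

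The cost is four degrees of freedom, a clinic code carried with the data, and wording. No additional patients are needed.

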### Statistical methods

#### Quantitative analysis

The longitudinal data will be analysed by variance analysis with repeated measurements; the nominal and ordinal scaled parameters will be evaluated by analysis of contingency tables; the subgroup analysis will be carried out with qui-square tests and t-tests.

The primary outcome *return to work* will be retrospectively captured with a questionnaire after 12 months. The rehabilitants will provide information regarding whether they returned to work after rehab and how much time passed between rehab and the return to work. The time until the return to work is collected in models of survival analysis for discrete times. The entire analysis will be carried out with SPSS 22.0.

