#### Secondary outcomes

After medical rehabilitation, a great number of patients return to work without major problems [46, 47]. To include the work-related effects from this study, further work-related outcomes will be considered.

*Work ability* will be measured with the Work Ability Score (WAS) of the Work Ability Index (WAI). This single item consists of work ability on a scale from 0 to 10, and a higher score indicates higher work ability. The WAS has been applied in numerous studies and has acceptable reliability and validity [48].

*Occupational stress* will be measured with the German version of SIBAR II and IV, and the overall burden and differentiated single burdens will be addressed [49].

The SPE scale in the German language considers the *subjective prognosis of gainful employment*. Three items estimate the occupational risk of the patients. Adding the single items to form a total score, the patients can be subdivided into two risk groups. This scale has been validated in a large sample and is also reliable. Thus, the items have a good ability to obtain the subjective prognosis of gainful employment [50, 51].

*Occupational changes* will be measured with single items, including job-preserving interventions and types of job loss [52].

Cancer-related *fatigue* will be measured by the EORTC-FA12, a questionnaire validated in a large international, multicentre study [53]. With the aid of twelve four-staged items (“not at all” to “very”), physical, emotional, and cognitive fatigue impairments are investigated. During a German study validating the questionnaire with breast cancer patients [54], a high consistency of the overall scale was observed; the subscale also shows good to high internal consistency.

*Depressive state* will be measured by the CES-D (Center for Epidemiological Studies Depression Scale, German version). The scale consists of 20 four-level scaled items regarding the presence and frequency of depressive symptoms. The evaluation is made according to a total score that can reach a maximum of 60 points. The higher the value is, the higher the expression of depressive symptoms. The CES-D is a reliable and valid questionnaire [55].

The *performance* in various areas of life will be assessed by three scales from 0 to 10 for the areas job, everyday life, and leisure. A high score implies high performance. The three single items are approved as a valid procedure for the determination of performance restrictions [52, 56].

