The extent of *physical activity* will be assessed in connection with the questionnaire of the Federal Health Survey by Menski, 1998 [57]. In addition, the use of health promotion services will be measured by a questionnaire from the Quality Community for Medical Rehabilitation [52, 56].

The moderating variable is comorbidity [58], as well as risk factors and sociodemographic variables [59]. Table 1 shows the set of the core instruments to be used in the study.

**Table 1 Tab1:** Core set of instruments used in the quantitative part of the study

Dimensions	Instruments	t_0_	t_1_	t_2_
Primary Outcome				
Restriction of Participation	IMET [42]	●		●
Disease-specific Quality of Life	EORTC-QLQ-C30 [60]	●	●	●
	EORTC-QLQ-BR23 [45]			
Return to Work	Single Items			●
Secondary Outcomes				
Ability to Work	Work Ability Score, WAS [61]	●		●
Occupational Stress	SIBAR, II and IV [49]	●		●
Subjective Prognosis of Employment	SPE-Scale [62]	●		●
Occupational Changes	Single Items from QGmR [52]			●
Fatigue	EORTC-FA 12 [54]	●	●	●
Depressive State	CES-D [55]	●	●	●
Performance in Various Areas of Life	QGmR [52]	●		●
Physical Activity	Federal Health Survey [57]	●		●
Use of Health Promotion Services	QGmR [52]	●	●	●
Moderating Variables				
Comorbidity	Single Items [58]	●		●
Living Habits	Single Items	●	●	●
Sociodemographic Data	Single Items [59]	●		●

t_0_ = baseline/right before rehabilitation; t_1_ = 3-week follow-up/right after rehabilitation; t_2_ = 12 months after t_1_

Outcomes that cannot change during rehabilitation will be measured in the beginning and regard only catamnesis. These include outcomes regarding everyday life and the domestic environment of the patients (social participation, efficiency and physical activity in daily life) or insignificantly changed outcomes, such as medically determined comorbidities.

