### Immediate expected results of the project

The use of ReNaApp for 12 months leads to clinically relevant and positive effects (pre-post-ES > 0.40) in different primary outcomes after rehab. In addition to a significant increase in social and work-related participation in the IG, breast cancer patients in the IG return faster and more often to work than patients following the standard aftercare programme. This is accompanied by lower indirect costs in the IG. Furthermore, the quality of life increases.

The extent of restriction in social and work-related participation and the quality of life of the control group are comparable to the conditions of the intervention group at the beginning of rehab. Additionally, the participants in the control group returned to work less often and later than participants in the intervention group.

Compared to the CG participants, IG participants using ReNaApp show significant positive effects in all secondary outcomes 1 year after rehab. This includes less physical, psychological and occupational stress as well as a better prognosis of employment and work ability.

Last, the intervention group shows differences compared to the control group regarding a significantly stronger extent of physical activity 1 year after rehab. Unlike the patients in the control group, the breast cancer patients in the intervention group more often engage in self-engaged fitness training or sports programmes though the ReNaApp; they practice significantly more endurance sports.

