### Limitations

First, it is possible that the disease worsens during and after rehabilitation. In this scenario, patients could contact their aftercare agents and review the personal aims and plans for physical activity and adapt them to the new situation.

In the technical part of the study, the risk of failure of the mobile application exists. In this case, we have the chance to consult our experts of IMIS and ITM to, e.g., provide new updates for the application.

Personal data will never be transferred from the application to the study leader or aftercare agents. ReNaApp keeps the information, statistics and documentation private.

To ensure equal treatment for the IG and CG, all characteristics of the participants (e.g., age, education) and the disease (e.g., disease severity, disease status, and comorbidity) will be documented and compared between the groups. If differences arise between the two groups, they will be comparably integrated in the analysis (e.g., as covariates in multivariate methods or by propensity score matching). Based on our present knowledge, we assume that structural changes in the context of this project are very unlikely.

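### Contingency tables for nominal and ordinal outcomes leave the collected t0 values, and usually the category order, unused, which costs power and can carry a remaining cohort difference into the 12-month comparison

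*Protocol article*

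**What the plan says.** The Quantitative analysis section names three routes for the between-group analyses.

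- Scores followed over time: "The longitudinal data will be analysed by variance analysis with repeated measurements".
- Categorical outcomes: "the nominal and ordinal scaled parameters will be evaluated by analysis of contingency tables". No time point, type of table test or baseline term is given.
- Return to work: "The time until the return to work is collected in models of survival analysis for discrete times".

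Several secondary outcomes could take the second route. For the SPE scale the Secondary outcomes section says: "Adding the single items to form a total score, the patients can be subdivided into two risk groups". Table 1 marks the SPE scale and physical activity at t0 and t2, and use of health promotion services at t0, t1 and t2. Occupational changes are marked at t2 only.

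On design, section A states that "recruitment of the control and intervention groups at the same time will not be possible": controls come first, the intervention group afterwards. Under Limitations, participant and disease characteristics are to be compared, and "If differences arise between the two groups, they will be comparably integrated in the analysis", with covariates or propensity score matching as examples. The sample-size section adds 10% for matching failures. For secondary outcomes, the expected results are that intervention participants, compared with controls, "show significant positive effects in all secondary outcomes 1 year after rehab".

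**The concern.** The expected result is directional: the intervention group should be better off at one year. An ordinary test of a group-by-category table asks whether the two distributions differ in any way. It spreads its power over all patterns of difference, including those that are not an improvement, and leaves out each patient's own starting value, which for several outcomes will already be on file.

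Two things are at stake. First, power: a real, ordered improvement in a secondary outcome may be missed although the data could show it. Second, protection against imbalance: no randomisation balances the cohorts at t0, so a difference present before the intervention can show up at 12 months. A plain two-way table has no term that would take it out. Whether this happens depends on how much difference is left after the adjustment or matching described under Limitations.

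**Working it through.** **The plan's own figure.** The article gives no power or error rate for the categorical analyses, so there is nothing to reproduce. I take from it only the analysed number: 370 × 0.7 / 1.1 = 235.5, that is 235 per group after dropout and matching losses. Whether 235 follows from its own inputs is a separate matter.

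**Assumptions, none of them in the article.** A latent normal variable with t0–t2 correlation 0.6, cut into k equally filled categories; two-sided alpha 5%; true effect 0.25 SD; t0 imbalance of 0.2 or 0.3 SD where stated. The simulations used 2,000 trials per setting. The analysis with t0 was a linear model on category scores, as a stand-in for the ordinal model.

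**Power, comparable cohorts, effect 0.25 SD.**

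- *Two categories, table.* Proportions 0.500 and Φ(0.25) = 0.599. SE = √[(0.250 + 0.240)/235] = 0.0457; z = 0.0987/0.0457 = 2.16; power = Φ(2.16 − 1.96) = 0.58. Simulated: 57–59%, against 66–67% with t0.
- *Five categories, table.* Control 0.200 in each; intervention 0.137, 0.170, 0.194, 0.222, 0.277. Noncentrality = 235 × Σ(p₁ − p₀)²/(p₁ + p₀) = 6.5 on 4 df; power 0.51. Simulated for 4 to 6 categories: 47–54%.
- *Five categories, trend test.* Difference in mean score 0.331, SE 0.1295, z = 2.56; power = Φ(2.56 − 1.96) ≈ 0.72. Simulated for 4 to 6 categories: 71–74%.
- *With t0 as covariate.* The residual SD falls by √(1 − 0.6²) = 0.8. Before categorising, z rises from 0.25/√(2/235) = 2.71 (power 0.77) to 2.71/0.8 = 3.39 (power 0.92). Categorising costs part of this. Simulated for 4 to 6 categories: 83–87%.

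**False rejection, no intervention effect.** With no cohort difference, every method rejects in about 5% of trials. With a difference, the result depends on how it behaves between t0 and t2.

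- *The imbalance regresses toward the mean.* A t0 shift of 0.2 SD becomes 0.6 × 0.2 = 0.12 SD at t2. Two categories: Φ(0.12) = 0.548, z = 1.04, rejection 0.18. Five categories: noncentrality 1.5, rejection 0.14. Simulated for 4 to 6 categories: table 12–16%, trend test 22–25%, with t0 5–6%. At 0.3 SD: table 25–29%, with t0 5–6%.
- *The shift persists in full.* Two categories at 0.2 SD: z = 1.73, rejection 0.41. Adjusting for t0 leaves 0.2 × (1 − 0.6) = 0.08 SD; before categorising, 0.08/(0.8 × 0.0923) = 1.08, rejection 0.19. At 0.3 SD, 0.12/0.0738 = 1.63, rejection 0.37. Simulated for four categories: table 35% and 71% at 0.2 and 0.3 SD; with t0 20% and 37%.

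Two consequences follow. Using order without t0 raises power but also sensitivity to imbalance. Using t0 alone is not enough if the cohorts differ persistently.

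**The case against.** The strongest reply is that the article does not commit to the weak test. Contingency-table analysis includes linear-by-linear trend tests and Mantel–Haenszel tests stratified by t0 category, and the choice may sit in a fuller document. A reader might infer a plain Pearson test on a 12-month table; the text fixes neither the time point nor the test. What stands is that the method named for all these outcomes has, in its standard form, no baseline term, while the same sentence keeps repeated measures for longitudinal data.

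Other stronger readings also fail.

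- *That the secondary hypothesis is improvement from t0.* The expected results describe a difference from controls at one year, which a group table does address. The case for t0 is precision and balance, not a different estimand.
- *That all these outcomes have a t0 value.* Occupational changes do not.
- *That several ordered categories are documented.* Most secondary outcomes are scores, and item formats for physical activity and service use are not given. The one documented grouping, SPE, has two levels. Order is irrelevant there and the gain is smaller. A change score would do worse: 64% against 73% for the table at 0.3 SD.
- *That false positives must occur.* Matching can precede a table, and the sample size allows for it. But the handling under Limitations is conditional, leaves covariates or matching open, and does not list the outcome's t0 value among its examples. It lowers the risk without removing it, and does not by itself recover the power lost by leaving out order and t0.

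**Conclusion.** The point holds in a limited form. For secondary outcomes analysed as categories and measured at t0, a standard table gives up information the study will already have. With 4 to 6 ordered categories the cost is about 35 points of power (about 50% against about 85%), of which order alone recovers about 22. With two categories it is about 8 points. These sizes rest on the assumed correlation, category counts and 0.25 SD effect.

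The effect on false positives is conditional: none when the cohorts are comparable; otherwise it depends on the difference that survives adjustment or matching. A reader might conclude that a t0 covariate restores the 5% level in every case. It does so only when the imbalance regresses toward the mean; under a persistent shift of 0.2 to 0.3 SD it still rejects in about 20% to 37% of null trials with four categories.

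Return to work under its survival model, and IMET and EORTC scales analysed as repeated scores, are untouched. The change is worth making before analysis, but no primary result is shown to depend on it.

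**What to change.** Replace the contingency-table clause with wording such as: ‘Ordinal outcomes at t2 are analysed by proportional-odds regression, and binary or nominal outcomes by logistic or multinomial logistic regression, with group, the t0 value of the same outcome where it is measured at t0, and the propensity covariates, or within the propensity-matched sample. Outcomes measured only at t2 are analysed with group and the propensity covariates. Contingency tables are descriptive.’

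State in advance which form of propensity handling applies, since t0 alone does not deal with a persistent cohort difference.

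The cost is analysis wording only: no new data are needed, and these models are available in the planned software. The downside is that the proportional-odds assumption must be checked.
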